### Sample size

2.5

The VAS score is the primary outcome measure of this trial. Based on the preliminary results from the research team’s earlier trials, the estimated VAS score for the treatment group after intervention is 1.6 ± 1 cm. Based on the data from relevant domestic clinical trials (26) and our preliminary exploratory trials, we predict that the VAS score for the control group is 2.41 ± 1.68 cm. The sample size ratio for the two groups is 1:1. Using PASS15 to calculate the sample size, with a two-sided test set at *α* = 0.05 and *β* = 0.10, and a test power of 0.9, at least 41 participants are needed in each group. Considering a 15% dropout rate, a total of 48 participants will need to be recruited for each group, resulting in a total of 96 participants required.

### Interventions

2.6

Participants in both groups of this study will be assessed on the first-day post-surgery, with treatment beginning on the second day and continuing for three consecutive days, totaling three sessions, with needles retained for 30 min each time. Subsequently, the treatments will be conducted three times a week for 4 weeks. Both treatments will be administered by trained acupuncturists who hold a valid practitioner certificate and have over 5 years of clinical experience, having undergone standardized training before the trial to ensure consistency. After discharge, patients need to undergo acupuncture treatment in the outpatient department; if numbness symptoms disappear, acupuncture treatment should be halted, and follow-up will continue per the experimental protocol.

#### Intervention group

2.6.1

**Acupoint prescription**: The umbilical acupoint selection is as shown in Figure 2; warm needle acupuncture points are: Qihai (CV 6), Guanyuan (CV 4), the affected side’s Zusanli (ST 36), and Yanglingquan (GB 34) acupoints.

**Needle type**: Disposable sterile acupuncture needles, Jiachen brand.

**Needling technique**: After disinfecting the umbilical area, a 0.25 mm × 25 mm ①②③④⑤ around the umbilicus (see Figure 2), angled radially outward from the center of the umbilicus at approximately 15°, with a depth of insertion around 20 mm, adjusted according to the patient’s body type. Needles are retained for 30 min. Details of selected acupoints are shown in Figure 2.

**Figure 2 fig2:**
[figure not shown]
Locations of acupoints.

After routine disinfection of CV 6, CV 4, the affected side’s ST 36, and GB 34, a 0.25 mm × 40 mm acupuncture needle is inserted directly, ensuring “Deqi” sensation is achieved at all acupoints. Once “Deqi” is reached, perform warm needle acupuncture at CV 6, ST 36, and GB 34; moxibustion uses moxa rolls with 1 cm lengths. During moxibustion, cardboard will be used as a shield to prevent burns.

#### Control group

2.6.2

Based on relevant literature and prior work, the electroacupuncture treatment methodology is as follows:

**Acupoint prescription:** Jiaji (X-B2) acupoints of the lumbar region (affected segment and adjacent segments), Shenshu (BL 23), Dachangshu (BL 25), the affected side’s Huantiao (GB 30), Zusanli (ST 36), Yanglingquan (GB 34), and Kunlun (BL 60).

**Needling technique:** After routine disinfection of the acupoints, standard needling is performed, ensuring “Deqi” sensation is achieved at all points. Electrical stimulation is then applied using pairs of needles at the following combinations: lumbar X-B2 and the affected side’s BL 25 – GB 30, ST 36 – GB 34. Continuous wave stimulation at a frequency of 2 Hz and an electrical current intensity ranging from 0.1 to 1.0 mA, adjusted to the patient’s tolerance, with needles retained for 30 min. Infrared lighting is also applied to the lumbar area during treatment.

**Treatment regimen:** Same as the experimental group.

The location of acupoints followed the World Health Organization’s Standard Acupuncture Locations (27).

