## Abstract

**Background:**

Postoperative residual numbness following lumbar disc herniation (LDH) surgery is a relatively common symptom. Existing drugs and physical therapies are not very effective. Acupuncture is effective for the treatment of LDH, but there are limited reports on its use for postoperative numbness. Based on clinical observations and literature review, we hypothesize that combining umbilical acupuncture (UA) with warm needle acupuncture(WA) may yield superior efficacy compared to electroacupuncture(EA) alone, enhancing immune function, promoting nerve recovery, and improving microcirculation through synergistic effects, thereby filling the gap in this treatment field.

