**Objective:**

This proposed trial aimed to evaluate the effectiveness and safety of UA (umbilical acupuncture) combined with WA (warm needle acupuncture) in treating residual numbness after LDH surgery. To verify the hypothesis that the combined method is superior to traditional electroacupuncture.

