### Randomization, allocation concealment, and blinding

2.4

Eligible patients will be randomly assigned to two groups: the treatment group (receiving warm needle acupuncture combined with Western medicine) and the control group (receiving electro-acupuncture). The randomization will be performed using the CHISS software for block randomization. The size of each block is n. Once the randomization scheme is generated, it will be kept by a third party independent of this study. To ensure allocation concealment, we use sealed opaque envelopes. These envelopes are prepared by an independent member of the research team, and participants draw an envelope randomly upon enrollment in the study to determine their treatment group. Clinical researchers will obtain the specific treatment plan for each patient through designated channels (such as by phone). Assessors will not be informed of the participants’ specific group assignments throughout the follow-up period. All assessment work will be carried out by assessors independent of the treatment process. These assessors will receive rigorous training before the study begins to ensure their standardized understanding and application of the VAS score, thereby ensuring the consistency and accuracy of the assessments. Assessors will be strictly restricted from accessing participants’ treatment group information throughout the follow-up period to maintain assessor blinding. Blind statistical analysis will also be implemented during the data aggregation and analysis phase, with statisticians remaining unaware of the participants’ treatment allocations to ensure the objectivity of the statistical analysis results. In the event of serious adverse events, emergency medical situations, or requests from participants, the sealed envelope containing the blinding information will be opened by an independent third party, and the reasons, time, and personnel involved in the unblinding will be recorded in detail and reported to the relevant committee promptly. Medical decisions will be made based on the unblinding results, and participants will be allowed to withdraw from the trial if necessary.

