### Western medicine treatment for all included patients

2.7

All patients included in this study received basic conventional Western medicine treatment: starting from the second day after surgery, they were administered anti-inflammatory and analgesic treatment (celecoxib capsules 200 mg, 1 capsule/time, 2 times/day) combined with neurotrophic treatment (mecobalamin tablets 0.5 mg, 1 tablet/time, 3 times/day) for 28 days (Note: Patients were required to continue treatment at the outpatient clinic after discharge. If their numbness symptoms disappeared, the basic Western medicine treatment was discontinued, which was recorded in the experimental protocol, and follow-up was continued according to the experimental protocol).

Drug Sources:

Mecobalamin Tablets: Produced by Jiangxi Qingfeng Pharmaceutical Co., Ltd., Approval Number: Guoyao Zhunzi H20051440.Celecoxib Capsules: Produced by Pfizer Pharmaceutical Co., Ltd., Approval Number: Guoyao Zhunzi J20120063.

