Drawing from the perspective of traditional Chinese medicine (TCM) pathogenesis and building on our prior clinical practice, we have, for the first time, applied UA combined with WA to treat postoperative numbness. UA is an emerging therapy established by [name]. Its theoretical basis is completely rooted in traditional Chinese culture. UA is different from traditional acupuncture, which is a therapeutic method to treat diseases by acupuncture at the umbilical point in a certain way based on the theory of bioholography (33). Compared with other acupuncture methods, umbilical acupuncture (UA) regulates the body’s qi and blood through the holographic reflex zones of the umbilicus, characterized by fewer acupoints and milder stimulation. Electro-acupuncture primarily exerts its effects through local nerve regulation, with relatively weak overall regulatory effects on systemic functions. Warm needle acupuncture that combines moxibustion and acupuncture has become increasingly popular due to its significant clinical efficacy and safety (34). This approach treats both the symptoms and the root causes, with a particular emphasis on addressing the underlying causes. Some studies have shown that WNA has better effects in relieving pain and promoting blood circulation compared with simple acupuncture or moxibustion (35). The therapeutic mechanism of WA is similar to the process of thermotherapy, in which a high-temperature area is formed locally in a tissue to promote metabolism, enlarge blood vessels, and reduce the excitability of peripheral nerves (34). The stimulus from needles in acupuncture involves a change of temperature and heat transfer through tissue. Both ambient and body temperatures influence the effect of acupuncture, this stimulus may result in the regulation of homeostasis (36). Comparing the physical efficiency of acupuncture needles regarding heat transfer with the daily energy consumption of a human body reveals an interesting and new aspect: Applying the normal energy consumption rate of a human body to CO3 domain volume results in 0.00003262 W, showing that the amount of energy conveyed by acupuncture needles is much higher than the body’s energy consumption and suggesting a strong stimulating effect in the regulation of homeostasis (36). UA and WA are widely used in clinical practice and have been proven safe (33).

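### The control regimen is electroacupuncture plus lumbar infrared, but the hypothesis names electroacupuncture alone, so the comparator is misnamed and the effect against electroacupuncture alone is not estimated

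*Protocol article*

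**What the plan says.** **What the control arm receives.** Section 2.6.2 introduces the control regimen with "Based on relevant literature and prior work, the electroacupuncture treatment methodology is as follows". It lists the acupoints and electrical settings and then adds: "Infrared lighting is also applied to the lumbar area during treatment". No infrared duration, distance or intensity is stated.

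**What the test arm receives.** Section 2.6.1 describes umbilical needling and warm needling, with the instruction to "perform warm needle acupuncture at CV 6, ST 36, and GB 34; moxibustion uses moxa rolls with 1 cm lengths". It mentions neither infrared nor lumbar heat.

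**What is common to both arms.** The session schedule is the same (2.6 and 2.6.2), and so is the drug background (2.7): "All patients included in this study received basic conventional Western medicine treatment".

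**How the comparator is named elsewhere.**
- Abstract, Background: the combination "may yield superior efficacy compared to electroacupuncture(EA) alone".
- Abstract, Objective: "To verify the hypothesis that the combined method is superior to traditional electroacupuncture".
- Section 1, last paragraph: comparison with electroacupuncture, with no mention of infrared.
- Section 2.4: "the control group (receiving electro-acupuncture", again without infrared.
- Section 2.12: the control mean is attached to a group labelled electroacupuncture.

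The Discussion gives the reasons for choosing an electroacupuncture control and does not mention infrared there either.

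**The concern.** Infrared is a physical treatment given to one randomised arm and absent from every statement of the research question. It cannot be dismissed as obviously inert on the document's own reasoning, because the Discussion explains the test treatment partly through heat: "The therapeutic mechanism of WA is similar to the process of thermotherapy". That sentence concerns warm needling, not lumbar infrared, so it does not show that infrared acts on numbness. It does show that the authors regard local heat as a plausible mechanism, and an unnamed heat source in the control arm therefore matters to interpretation.

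At stake is the wording of the conclusion. A report that follows the Abstract would claim a benefit, or no benefit, over electroacupuncture alone. No participant is assigned to electroacupuncture without infrared, so that contrast is not observed. A reader of the Abstract would not know that infrared had been given.

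**Working it through.** This is mainly a comparison of passages, with a little algebra to show what is lost and in which direction.

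**Step 1. The arms side by side.**

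| Component | Test arm (2.6.1) | Control arm (2.6.2) |
|---|---|---|
| Needling | Umbilical points; CV 6, CV 4, ST 36, GB 34 | Lumbar Jiaji, BL 23, BL 25, GB 30, ST 36, GB 34, BL 60 |
| Electrical stimulation | None stated | 2 Hz, 0.1 to 1.0 mA |
| Moxa heat | CV 6, ST 36, GB 34 | None stated |
| Lumbar infrared | None stated | Yes |
| Drugs and schedule | Same | Same |

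The design compares two packages. Infrared is the one control component that the hypothesis, objective and arm description leave out.

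**Step 2. What is estimated.** Let the mean numbness VAS (lower is better) be T in the test arm, EI under electroacupuncture plus infrared, and E under electroacupuncture without infrared, all on the same drug background.

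- Estimated by the trial: D = EI − T.
- Asked in the Abstract Background: E − T.
- Identity: E − T = (EI − T) + (E − EI) = D + δ, where δ = E − EI is the benefit of adding infrared to electroacupuncture.

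The trial gives D. It has no arm from which δ could be learned, and the document gives no value for it.

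**Step 3. Direction.**
- δ = 0 (infrared neutral): D answers both questions.
- δ > 0 (infrared helpful): D understates the benefit over electroacupuncture alone. If D is shown to be positive, D + δ is positive as well, so superiority is conservative.
- D near 0: the benefit over electroacupuncture alone is about δ, which may be nil or positive. A null result does not settle the stated hypothesis.
- δ < 0 (infrared harmful to numbness): only then could superiority over the package overstate superiority over electroacupuncture alone. Nothing in the document suggests this.

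**Step 4. The planning difference.** Sections 2.5 and 2.12 give 2.41 cm for control and 1.6 cm for treatment, and 2.41 − 1.6 = 0.81 cm, as stated. Section 2.5 takes the control value from domestic trials and the team's exploratory work, without saying whether infrared was used.
- If 2.41 cm already includes infrared, the planned D stays at 0.81 cm and power is unaffected.
- If it does not, the expected D is 0.81 − δ.

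Purely as an illustration, with δ *assumed* to be 0.1, 0.2 or 0.3 cm, D becomes 0.71, 0.61 or 0.51 cm. Using the stated SDs (1.0 and 1.68), SE = √((1.0² + 1.68²)/41) = 0.305 cm. Two-sided Welch power with 41 per arm goes from about 74% at 0.81 cm to about 63%, 50% and 38%. The 74% differs from the 90% claimed because the stated 41 per arm does not reproduce: the stated inputs give 62 (normal approximation) or 63 (Welch). That is a separate matter and neither supports nor weakens this point.

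**The case against.** The strongest reply is that infrared sits inside the protocol's own definition of the electroacupuncture method in 2.6.2. The Abstract objective, the Introduction and sections 2.4 and 2.12 say electroacupuncture without *alone*, so the trial does compare the new regimen with electroacupuncture as this protocol delivers it. On this view the mismatch is one word in the Abstract Background. Even that word may only contrast one acupuncture modality with two combined, since both arms also take celecoxib and mecobalamin.

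Much of this stands. It shows that the comparison is valid and that the contradiction in wording is sharpest in one place. It does not remove the point. The drugs are common to both arms, whereas infrared is not. A reader who meets only the hypothesis, objective or arm description has no way to learn that the comparator includes it.

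Four stronger readings are tempting but not supported:
- *That the trial cannot answer its question.* Randomisation supports the package comparison, and with neutral or helpful infrared a superiority result carries over to electroacupuncture alone.
- *That infrared accounts for some given share of the 0.81 cm.* No passage gives an infrared effect, and the control mean may already include it.
- *That the test arm goes without heat.* It receives moxa heat at CV 6, ST 36 and GB 34.
- *That heat injury is captured in one arm only.* Section 2.9 names skin injury after moxibustion and nothing for infrared, but its list is one of examples and all adverse events are graded by CTCAE.

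**Conclusion.** The point holds as a mismatch between the stated comparator and the delivered one. The trial estimates the effect of umbilical plus warm needle acupuncture against electroacupuncture plus lumbar infrared. It does not estimate the effect against electroacupuncture alone, and a null result would leave that question open. A superiority result would be conservative for it, on the assumption that infrared is neutral or helpful.

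The gap between the two effects equals the unknown benefit of adding infrared to electroacupuncture. The document does not allow it to be sized, and the power figures above illustrate assumed values only. The conclusion rests on 2.6.1 being complete, that is, on the test arm receiving no infrared. The matter should be corrected because it changes what may be concluded, but it does not invalidate the design.

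**What to change.** Reconcile the Abstract (Background and Objective), the last paragraph of the Introduction, section 2.4 and section 2.12 with section 2.6.2. If infrared stays in one arm only, name the comparator as electroacupuncture plus lumbar infrared in the hypothesis, objective, arm description and planned conclusion, and drop *alone*. Whether infrared belongs in the regimen is for the sponsor to decide.

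This changes wording only and leaves the randomisation and the analysis model as they are. Section 2.14 says that enrolment is under way, so it should be settled before results are reported. The downside is a narrower claim: the trial would speak to the package actually given and not to electroacupuncture by itself.

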### Western medicine treatment for all included patients

2.7

All patients included in this study received basic conventional Western medicine treatment: starting from the second day after surgery, they were administered anti-inflammatory and analgesic treatment (celecoxib capsules 200 mg, 1 capsule/time, 2 times/day) combined with neurotrophic treatment (mecobalamin tablets 0.5 mg, 1 tablet/time, 3 times/day) for 28 days (Note: Patients were required to continue treatment at the outpatient clinic after discharge. If their numbness symptoms disappeared, the basic Western medicine treatment was discontinued, which was recorded in the experimental protocol, and follow-up was continued according to the experimental protocol).

Drug Sources:

Mecobalamin Tablets: Produced by Jiangxi Qingfeng Pharmaceutical Co., Ltd., Approval Number: Guoyao Zhunzi H20051440.Celecoxib Capsules: Produced by Pfizer Pharmaceutical Co., Ltd., Approval Number: Guoyao Zhunzi J20120063.

### Outcomes measurement

2.8

#### Primary outcome

2.8.1

Numbness VAS Score: Patients are asked to mark their level of numbness on a 10 cm horizontal line. A higher score indicates a more severe degree of numbness. A score of 0 indicates no numbness; 1–3 indicates mild numbness that does not affect daily life; 4–6 indicates moderate numbness with a decreased quality of life but still self-care ability; 7–9 represents severe numbness with loss of self-care ability; and a score of 10 indicates intense, unbearable numbness (see Figure 3).

**Figure 3 fig3:**

Visual analog scale for numbness.

#### Secondary outcome

2.8.2

Nylon Filament Test (10 g Monofilament Test): A 10 g monofilament is used to stroke the skin area where the patient feels numb. The numb skin area is stroked 10 times, and the number of strokes perceived is observed and recorded. Perceiving 7–10 strokes is considered normal, 1–6 strokes is considered reduced sensation, and 0 strokes is considered absent sensation. The researcher records these as 3 points, 2 points, and 1 point, respectively. The study indicates that tactile static testing using a 10 g monofilament demonstrates the highest sensitivity for detecting superficial sensory disturbances. It can be recommended as the most sensitive single testing tool (28).

Pinprick Test (40 g Pressure Pinprick Test): A blunt-tipped pressure needle is used to apply a constant force to the patient’s numb area. The presence or absence of pain is observed and recorded, with pain scored as 1 point and no pain scored as 0 points. The experiment differentiates neuropathic pain from sensory loss by assessing Aδ fiber function, with sensitivity and specificity ranging from 68 to 85% and 79 to 92%, respectively (29). The test demonstrates good reproducibility (ICC = 0.89) in the assessment of postoperative neuropathy (30).

Other secondary indicators: JOA (Japanese Orthopedic Association) Score, a study mentioned that the JOA scoring system was used to evaluate 89 patients who underwent lumbar decompression surgery, and it was found that 30.3% of patients still had mild lower extremity pain/numbness and 14.6% of patients still had gait disturbances 2 years after the surgery. This indicates that the JOA scoring system can effectively identify residual symptoms after surgery (31). Traditional Chinese Medicine Syndrome Score, the TCM Syndrome Score does not focus solely on individual symptoms, but rather considers multiple symptoms and signs comprehensively, providing a more holistic assessment of the patient’s condition, it has high effectiveness in evaluating treatment outcomes (32). Additionally, Lower Limb Electromyography (H-reflex difference, F-wave conduction velocity, and latency), VAS Score, SF-36 (Short Form 36 Health Survey Questionnaire). The evaluation time points are detailed in Table 1.

**Table 1 tab1:** Timeline for the collection of evaluation indicators.

Observation indicators	Pretreatment	Treatment stage		Follow-up phase	
	Baseline (in geodetic survey)	1 week	4 weeks	12 weeks after treatment	24 weeks after treatment
General information	√				
Numbness VAS score	√	√	√	√	√
Nylon rope test	√	√	√		
Needle punching test	√	√	√		
JOA score	√	√	√	√	√
Lower Limb EMG	√	√	√		
Chinese medicine evidence score	√	√	√	√	√
SF-36 (Quality of Life Scale)	√	√	√	√	√
VAS score	√	√	√	√	√
Safety observations		√	√	√	√

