**Methods:**

This proposed study is a single-center, single-blind, prospective, randomized controlled trial (RCT) involving patients with LDH who were hospitalized and underwent percutaneous endoscopic lumbar discectomy (PELD) at our hospital. Patients meeting the inclusion criteria will be randomly assigned to either the treatment group (umbilical acupuncture combined with warm needle acupuncture) or the control group (electroacupuncture). The participants will be assessed on the first day after surgery, and acupuncture treatment will begin on the second day and continue for three consecutive days, with each session lasting 30 minutes. After that, the treatment mixture was changed three times a week for four weeks. All patients received standard Western medical drug treatment. After the treatment is concluded, a six-month follow-up will be conducted. The primary efficacy indicator will be the visual analog scale (VAS) score for numbness. The secondary efficacy indicators will include the 10 g monofilament test, 40 g pressure acupuncture sensation examination, Japanese Orthopedic Association (JOA) score, lower limb electromyography (H-reflex differences, F-wave conduction velocity, and latency), VAS score, traditional Chinese medicine symptom scoring, and Short Form 36-Health Survey (SF-36) score. Any adverse events occurring during the trial will be recorded. The data will be analyzed according to a predefined statistical analysis plan.

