### Statistical analysis

2.12

Sample size calculation was performed using PASS software (version 15.0, NCSS LLC). Based on preliminary data, the estimated mean (standard deviation) of the VAS numbness score after intervention for the treatment group (UA + WA) is 1.6 ± 1.0 cm, and for the control group (electroacupuncture) it is 2.41 ± 1.68 cm. To detect a between-group difference of 0.81 cm with 90% power (*β* = 0.10) and a two-sided *α* of 0.05, at least 41 participants are required in each group. Considering a 15% dropout rate, the final sample size is set at 48 participants per group (96 participants in total). This calculation complies with the CONSORT guidelines for randomized controlled trials.

All analyses will follow the intention-to-treat (ITT) principle, including all randomized participants. Additionally, for sensitivity analysis, a per-protocol set (PPS) analysis will be conducted, excluding participants with major protocol deviations (e.g., fewer than 8 acupuncture sessions, and use of prohibited medications). The primary outcome, the change in VAS numbness score over time points (baseline, 1 week, 4 weeks, 12 weeks, 24 weeks), will be assessed using a linear mixed-effects model (LMM). The model will include group, time, group-by-time interaction, and baseline VAS score as fixed effects. Random intercepts and slopes will account for within-individual variability. Missing data will be handled using multiple imputation (MI) with fully conditional specification (FCS) in SAS 9.4 (SAS Institute), generating 10 imputed datasets. Estimates will be combined according to Rubin’s rules. Sensitivity analysis will compare MI with the last observation carried forward (LOCF). For secondary outcomes with continuous variables (e.g., JOA, SF-36), the same LMM structure as the primary outcome will be used. For ordinal/categorical variables (e.g., TCM syndrome score), proportional odds logistic regression or generalized estimating equations (GEE) will be applied to longitudinal ordinal data. For binary outcomes (e.g., adverse events), comparisons between groups will be made using the chi-square test or Fisher’s exact test (for small sample sizes). Risk ratios (RR) and 95% confidence intervals (CI) will be reported.

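### The monofilament test records a 0–10 count, but the outcome defined from it has only three levels; analysing that score would lose power on this secondary outcome, by an amount the document cannot fix

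*Protocol article*

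**What the plan says.** The abstract lists the test among the secondary outcomes: "The secondary efficacy indicators will include the 10 g monofilament test, 40 g pressure acupuncture sensation examination". Section 2.8.2 describes it in three steps.

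- Measurement: "The numb skin area is stroked 10 times, and the number of strokes perceived is observed and recorded".
- Grouping: "Perceiving 7–10 strokes is considered normal, 1–6 strokes is considered reduced sensation, and 0 strokes is considered absent sensation".
- Scoring: "The researcher records these as 3 points, 2 points, and 1 point, respectively".

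Table 1 schedules the test at baseline, week 1 and week 4 only.

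Section 2.12 does not name the monofilament test. It gives one rule for continuous secondary outcomes, "For secondary outcomes with continuous variables (e.g., JOA, SF-36), the same LMM structure as the primary outcome will be used", and another for ordinal or categorical ones, under which "proportional odds logistic regression or generalized estimating equations (GEE) will be applied to longitudinal ordinal data". A 1/2/3 score falls under the second rule. Nothing in the article says that the count itself will be analysed.

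**The concern.** The score is much coarser than the measurement behind it. Ten possible improvements of one stroke (0 to 1, 1 to 2, up to 9 to 10) reduce to two that change the score: 0 to 1 and 6 to 7. A patient who goes from feeling one stroke to feeling six gains nothing. A patient who goes from six to seven is scored as recovered. A patient at seven or more cannot improve at all. Such patients may well be enrolled, because section 2.3.1 selects on the numbness VAS and not on the monofilament count.

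Section 2.8.2 justifies the test by its sensitivity, and the three-level score works against that reason. The pinprick test is scored only 0 or 1, so the stroke count is the one graded result among the two bedside sensory examinations. At stake is the chance of detecting a sensory difference between the groups on this secondary outcome.

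**Working it through.** **What the article fixes.** The raw measure is a count from 0 to 10. The cut-points are 7–10, 1–6 and 0, and the scores are 3, 2 and 1. Section 2.5 gives 41 evaluable and 48 recruited per group, "with a two-sided test set at *α* = 0.05".

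**What it does not fix.** It states no distribution, spread, effect size or power for the monofilament test. The only sizing is for the numbness VAS, so there is no figure for this outcome to reproduce. The 41 and 48 are used here only as group sizes.

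**Assumptions for the check.**

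- Each patient's count is beta-binomial on 10 strokes, with mean per-stroke probability μ and within-patient correlation ρ. The beta parameters are a = μ(1 − ρ)/ρ and b = (1 − μ)(1 − ρ)/ρ.
- Control μ runs from 0.2 to 0.8 (mean 2 to 8 strokes), and ρ is 0.1, 0.2, 0.3 or 0.5. That is 7 × 4 = 28 scenarios for each group size.
- In each scenario the treated-group μ is set so that the count analysis has about 80% power.
- Both variables are tested with a tie-corrected, two-sided Wilcoxon rank-sum test at one time point. For two groups this is essentially the proportional-odds score test.
- There are 6,000 simulated trials per scenario, so the Monte Carlo standard error near 80% power is √(0.8 × 0.2/6000) ≈ 0.005.

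**One scenario in full.** Take 48 per group, ρ = 0.2, and μ of 0.4 (control) against 0.555 (treated). The probabilities of scores 1, 2 and 3 are 0.08, 0.73 and 0.19 in the control group, and 0.02, 0.58 and 0.39 in the treated group. Most patients in both groups sit in the middle category, where differences in count are invisible. Power is 0.800 on the count and 0.669 on the score, a loss of 0.131.

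**Selected scenarios, 48 per group.**

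| ρ | control μ | treated μ | power, count | power, score | loss |
|---|---|---|---|---|---|
| 0.5 | 0.2 | 0.380 | 0.782 | 0.768 | 0.014 |
| 0.3 | 0.2 | 0.350 | 0.803 | 0.743 | 0.060 |
| 0.3 | 0.5 | 0.672 | 0.801 | 0.682 | 0.119 |
| 0.3 | 0.6 | 0.759 | 0.797 | 0.636 | 0.161 |
| 0.1 | 0.3 | 0.422 | 0.802 | 0.537 | 0.265 |
| 0.1 | 0.8 | 0.888 | 0.801 | 0.408 | 0.394 |

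**Range over both group sizes, in percentage points.**

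- Control mean 2–6 strokes, ρ = 0.2–0.3: 6 to 16.
- Control mean 2–6 strokes, ρ = 0.1: 14 to 29.
- Control mean 2–6 strokes, ρ = 0.5: 1 to 14.
- Control mean 7–8 strokes, any ρ: 20 to 39.

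The score lost power in every scenario. The loss is small when counts are widely spread and many patients feel no strokes, because the score then still separates the groups at its lower cut. It is large near the ceiling: in the last row of the table, 81% of control patients already hold the top score.

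**The case against.** **The count is kept.** The article says that "the number of strokes perceived is observed and recorded". A reader might infer from the scoring rule that the count is thrown away; the text does not support that. Information is lost only if the score alone is analysed, and section 2.12 does not name the variable. This part of the objection stands and makes the point conditional. It does not remove it: the score is the only outcome the article defines from this test, so this is a stated choice and not a detail left to an analysis plan.

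**The size is assumed.** This stands. A reader might want one moderate figure, such as 10 to 19 points, but only 10 of the 28 scenarios at 48 per group fall in that band, and the article offers nothing to choose among them. The simulation also uses a single time point without baseline adjustment, so a longitudinal model would give different absolute powers.

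**Three levels are clinically readable, and ordinal methods are planned.** Both are true. The planned methods are valid for the score, but they cannot recover differences that it has merged.

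**The test's importance can be overstated.** A reader might take it as the decisive objective check on a self-reported primary outcome. The article does not support that. Assessors are blinded, but feeling a stroke is still the patient's own response, and lower-limb electromyography (H-reflex difference, F-wave velocity and latency) is also planned.

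**Conclusion.** The point holds in conditional form. The defined score merges counts of 1–6 and of 7–10. If it is the variable analysed, as the text most naturally reads, it gives less power than the count already recorded. The direction was the same in all scenarios tried. The size, about 1 to 39 points from a count analysis with about 80% power, rests wholly on the assumed beta-binomial distribution and effect and should be quoted only with those assumptions.

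Severity is low. This is one of several secondary outcomes, the trial was not sized on it, and nothing here affects the validity of the score analysis or the primary conclusion.

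**What to change.** In section 2.8.2, name the 0–10 stroke count as the monofilament outcome. In section 2.12, state its model: for example, a longitudinal ordinal or beta-binomial model over weeks 1 and 4, adjusted for the baseline count. Report normal, reduced and absent sensation as a descriptive table by group and visit.

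In section 2.10, make sure the count itself, and not only the derived score, is carried from the case report form into the analysis dataset. Section 2.8.2 speaks of recording both, so which of them reaches the dataset is at present open. Settling it before the data are examined also rules out a later choice between count and score.

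The cost is small. No new measurement is needed. Enrolment has begun (section 2.14), so the change should be made as a documented amendment, with ethics approval where section 2.1 requires it. The main result also becomes somewhat harder to summarise clinically, which the descriptive table largely offsets.
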